## 4. Risks and Harms

The main risk of the project is related to the use rate of the teleconsulting system by primary care professionals, which might be lower than expected. However, the experience gathered during the BRAHIT feasibility test based on over 60 patients managed using the teleconsultation approach described above indicates that the project is feasible in the planned period for its execution.

Other risks include changing the BRAHIT project team at the institutional level; this risk is deemed low, as they are professionals admitted through public examination in their home institutions. The interaction of graduate students with pre-planned teaching programs will reduce the project risk. The study intervention has a low yield of inflicting harm on participants. Teleconsultations may prevent patients from being seen by a specialist; this has been described as a risk in systematic reviews [51], although the issue has not yet been addressed in studies to date.

## 5. Discussion

The study addresses a knowledge gap relating to the effectiveness and safety of teleconsultation support for primary care physicians. The study topic is its application to support the clinical management in primary care services of patients with uncompensated heart failure who were recently discharged from hospitals in Rio de Janeiro, Brazil.

E-health tools, including telemedicine, teleconsultation, and telemonitoring, have been used increasingly, especially since the COVID-19 pandemic. Aspects such as ethical and medical-legal issues of e-health interventions are currently under study and debate [52], so it is justified that we carefully assess the effectiveness of these interventions to allow a proper evaluation of risk-to-benefit ratio.

We expect to analyse the effects of the teleconsultation support from cardiologists to primary care physicians on patient-relevant outcomes, such as all-cause mortality, hospital readmission, patient-reported quality of life, symptom frequency, serious adverse events, and compliance with guidelines by the primary care physicians. The study will address these multiple outcomes using a pragmatic approach recommended for the study of public health interventions [53,54,55].

Many studies highlight difficulties concerning diagnosis and compliance with heart failure treatment guidelines in primary care settings [56,57,58,59,60]. We believe these hurdles may be due to primary care physicians’ competence gap in managing heart failure patients.

Our experience from a still unpublished feasibility test indicated improvement opportunities, reinforcing the need described in the reviewed literature [13,14] for a clinical trial with a rigorous methodology to assess teleconsultation effectiveness using patient-relevant outcomes.

Some factors limit our study. Although designed as a randomised clinical trial, many pragmatic features place it at an intermediate point within the PRECIS-2 explanatory–pragmatic continuum [22]. We anticipate some heterogeneity in the cluster population. Our eligibility criteria are broad and include all primary care practices from Rio de Janeiro, regardless of the primary care model (family health strategy versus non-family strategy organisations); we used stratification techniques to minimise this effect. We will include all adult patients with confirmed heart failure of all aetiologies, regardless of comorbidities or clinical status. We will analyse data according to the intention-to-treat principle, despite the primary care physicians’ adherence to the intervention. Although these factors aim to increase our findings’ external validity, they may undermine statistical analysis. We will rely on stratification and randomisation to overcome bias and anticipate data loss through recruitment and retention monitoring.

Notwithstanding its limitations, our research may produce valid and reliable data to guide recommendations for public policy implementation that may lead to primary care quality improvement in heart failure management and possibly other chronic conditions, in line with recommendations from national and global institutions [10,61] which advocate the use of e-Health tools to improve primary care quality.

## 6. Conclusions

Teleconsultation between specialists and primary care physicians may have a potential role in improvement of heart failure management in primary care. If proven effective, the collaboration model can be further studied and utilised for other conditions, especially in locations with scarce professional human resources.

## Figures and Tables

**Figure 1 ijerph-20-05933-f001:**
[figure not shown]
Study workflow.

**Table 1 ijerph-20-05933-t001:** Participant Timeline.

Enrolment	T_−1_	T_0_	T_6_ (Close-Out)
General practice stratification and randomisation	X		
Patient eligibility screening using municipality data	X		
Invitation to participate (patient)	X		
Invitation to participate (physician)	X		
Informed consent (patient and physician)	X		
Patient allocation according to practice randomisation		X	
Intervention			
Intervention group		Teleconsultation support for the practice’s physicians (first contact and on demand)	
Control group		Usual care with follow-up of outcomes	
Assessments		T_0_	T_6_ (close-out)
1—Readmissions and Mortality (reports)			X
2—Days Alive Out of Hospital (DAOH)			X
3—Frequency of Serious Adverse Events			X
4—Symptoms Frequency and Severity		X	X
5—Quality of Life		X	X
6—Adherence to Prescribing Guidelines		X	X

**Table 2 ijerph-20-05933-t002:** Baseline Variables.

N	Variable	Field Type	Choices, Calculations, or Labels
Physician Variables—direct inquiry			
1	Name	Text	-
2	Social Identification Number (CPF)	Text	-
2	Completed years since graduation	Number	-
3	Specialisation	Option	Any/Family Medicine/Other
4	Completed years in primary care	Number	-
5	Completed years in the current practice	Number	-
6	Enrolled in a residency program	Options	No/Preceptor/1st year Resident/2nd year Resident/3rd year Resident/Program
Patient Variables—primary care electronic health record report			
1	Name	Text	-
2	Social identification number (CPF)	Text	-
3	National Health System identification number (CNS)	Text	-
4	Primary care practice	Text	
5	Gender	Options	Feminine/Masculine/Nonbinary
6	Race	Options	White/Black/Brown/Other
7	Birth date	Date	-
8	Weight (Kg)	Number	-
9	Height (cm)	Number	-
10	NYHA status	Options	1 to 4
11	Systolic blood pressure	Number	-
12	Diastolic blood pressure	Number	-
13	Heart rate	Number	-
14	Dyspnoea	Option	Yes/No
15	Leg Swelling	Option	Yes/No
16	Dizziness	Option	Yes/No
17	Fatigue	Option	Yes/No
18	Orthopnoea or paroxysmal nocturnal dyspnoea	Option	Yes/No
19	Syncope	Option	Yes/No
20	Typical chest pain	Option	Yes/No
21	Jugular vein distension	Option	Yes/No
22	Pulmonary rales	Option	Yes/No
23	ACE-I (names)	Option	ACE-I names
24	ACE-I dose	Number	-
25	ARB (names)	Option	ARB names
26	ARB dose	Number	-
27	Beta-blockers (names)	Option	BB Names
28	Beta-blockers dose	Number	-
29	Spironolactone	Option	Yes/No
30	Spironolactone dose	Number	-
31	Furosemide	Option	Yes/No
32	Furosemide dose	Number	-
33	Digoxin	Option	Yes/No
34	Digoxin dose	Number	-
35	Syncope	Option	Yes/No
36	Hypertension	Option	Yes/No
37	Diabetes	Option	Yes/No
38	Dyslipidaemia	Option	Yes/No
39	Coronary artery disease	Option	Yes/No
40	Peripheric artery disease	Option	Yes/No
41	Cerebrovascular disease	Option	Yes/No
42	Atrial fibrillation	Option	Yes/No
43	Chagas disease	Option	Yes/No
44	Pulmonary chronic obstructive disease	Option	Yes/No
45	Creatinine	Number	-
46	Echocardiogram ejection fraction	Number	-

ACE-I—angiotensin conversion enzyme inhibitors; ARB—angiotensin receptor blockers; BMI—body mass index; NYHA—New York Heart Association.

## Data Availability

The data presented in this study are available on request from the corresponding author. The data are not publicly available due to sensitive content.

## Appendix A. Symptom Status Questionnaire—Heart Failure

Instructions: Please read each statement carefully, then circle the number that best describes your condition or how much you were bothered by these symptoms during the past four weeks.

1. Did you have shortness of breath during the daytime?

0. No (If your answer is no—please go to question 2)

1. Yes (If your answer is yes—please fill out 1a, 1b, 1c)

  1a. How often?

  (1) Less than once per week   (2) 1–2 times per week   (3) 3–5 times per week   (4) Nearly daily

  1b. How severe?

  (1) Slight   (2) Moderate   (3) Severe   (4) Very severe

  1c. How much did it distress or bother you?

  (0) Not at all   (1) A little bit   (2) Somewhat   (3) Quite a bit   (4) Very much

2. Did you have shortness of breath when you lay down?

0. No (If your answer is no—please go to question 3)

1. Yes (If your answer is yes—please fill out 2a, 2b, 2c)

  2a. How often?

  (1) Less than once per week   (2) 1–2 times per week   (3) 3–5 times per week   (4) Nearly daily

  2b. How severe?

  (1) Slight   (2) Moderate   (3) Severe   (4) Very severe

  2c. How much did it distress or bother you?

  (0) Not at all   (1) A little bit   (2) Somewhat   (3) Quite a bit   (4) Very much

3. Did you have fatigue or lack of energy?

0. No (If your answer is no—please go to question 4)

1. Yes (If your answer is yes—please fill out 3a, 3b, 3c)

  3a. How often?

  (1) Less than once per week   (2) 1–2 times per week   (3) 3–5 times per week   (4) Nearly daily

  3b. How severe?

  (1) Slight   (2) Moderate   (3) Severe   (4) Very severe

  3c. How much did it distress or bother you?

  (0) Not at all   (1) A little bit   (2) Somewhat   (3) Quite a bit   (4) Very much

4. Did you have chest pain?

0. No (If your answer is no—please go to question 5)

1. Yes (If your answer is yes—please fill out 4a, 4b, 4c)

  4a. How often?

  (1) Less than once per week   (2) 1–2 times per week   (3) 3–5 times per week   (4) Nearly daily

  4b. How severe?

  (1) Slight   (2) Moderate   (3) Severe   (4) Very severe

  4c. How much did it distress or bother you?

  (0) Not at all   (1) A little bit   (2) Somewhat   (3) Quite a bit   (4) Very much

5. Did you have leg or ankle swelling?

0. No (If your answer is no—please go to question 6)

1. Yes (If your answer is yes—please fill out 5a, 5b, 5c)

  5a. How often?

  (1) Less than once per week   (2) 1–2 times per week   (3) 3–5 times per week   (4) Nearly daily

  5b. How severe?

  (1) Slight   (2) Moderate    (3) Severe    (4) Very severe

  5c. How much did it distress or bother you?

  (0) Not at all   (1) A little bit   (2) Somewhat   (3) Quite a bit   (4) Very much

6. Did you have difficulty sleeping at night?

0. No (If your answer is no—please go to question 7)

1. Yes (If your answer is yes—please fill out 6a, 6b, 6c)

  6a. How often?

  (1) Less than once per week    (2) 1–2 times per week   (3) 3–5 times per week   (4) Nearly daily

  6b. How severe?

  (1) Slight   (2) Moderate   (3) Severe   (4) Very severe

  6c. How much did it distress or bother you?

  (0) Not at all   (1) A little bit   (2) Somewhat   (3) Quite a bit   (4) Very much

7. Did you have dizziness or loss of balance?

0. No (If your answer is no—just check No and stop here)

1. Yes (If your answer is yes—please fill out 7a, 7b, 7c)

  7a. How often?

  (1) Less than once per week   (2) 1–2 times per week   (3) 3–5 times per week   (4) Nearly daily

  7b. How severe?

  (1) Slight   (2) Moderate   (3) Severe   (4) Very severe

  7c. How much did it distress or bother you?

  (0) Not at all   (1) A little bit   (2) Somewhat   (3) Quite a bit   (4) Very much

Scoring method and interpretation

1. Sum all scores of a, b, and c for each symptom. For example, dizziness score = 7a + 7b + 7c.

2. If a person did not experience the symptom, score 0 for all the symptom items.

3. Thus, the possible score range for each symptom will be 0 to 12. These seven combined scores will be used to obtain Cronbach’s alpha.

4. To obtain the total symptom score, sum all seven combined scores. Thus, the total possible score range is 0 to 84 (12*7).

5. Higher scores indicate more severe heart failure symptoms.

Copyright, 2014 [name], PhD, [name], PhD, and [name], PhD

## Appendix B. Treatment Adherence Score

**Table A1 ijerph-20-05933-t0A1:** Treatment Adherence Score.

**Item/Points**	**2**	**1**	**0**
ACE-I use	Target Dose	Used below 50% of Target Dose [49]	Not used
OR			
ARB use	Target Dose	Used below 50% of the Target Dose	Not used
AND			
Beta-blockers use	Target Dose	Used below 50% of the Target Dose	Not used
Spironolactone use	Not indicated or Target Dose	Used below 50% of the Target Dose	Not used

Range: 0 to 8 points. ACE-I—Angiotensin-converting Enzyme Inhibitor; ARB—Angiotensin Receptor Blocker.

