### 3.2. Outcomes

The primary outcome will be a composite of all-cause mortality or one or more hospital readmissions. Any pre-hospital or hospital stay because of heart failure will be considered as a readmission [42,43]. Secondary outcomes will include hospital-free days within 180 days [44,45,46], serious adverse events (defined as any adverse event that results in death, is life-threatening, requires hospitalisation or prolongation of existing hospitalisation, or results in persistent or significant disability or incapacity, measured in municipality admission reports), frequency and intensity of heart failure signs and symptoms, measured using the Symptom Status Questionnaire—Heart Failure—Brazilian Version (Appendix A) [40,41], computed as a 0 to 84 score, and health-related quality of life, measured using the EQ-5D-5L questionnaire [37,38] scored using a value set validated for the Portuguese version [39] on a visual-analogic scale (0 to 100).

An exploratory outcome will be physicians’ adherence to guidelines, comparing prescription data to guidelines and quality standards using a compliance score (Table A1 in Appendix B) [47,48,49,50]. We will measure all outcomes at the patient level, at baseline when meaningful, and after six months of allocation.

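### The Treatment Adherence Score has no category for doses from 50% to just under target, so an exploratory outcome cannot be computed as written for patients in that band

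*Protocol article*

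**What the plan says.** Section 3.2 (Outcomes) introduces the measure: "An exploratory outcome will be physicians’ adherence to guidelines, comparing prescription data to guidelines and quality standards using a compliance score". It refers the reader to Table A1 in Appendix B for the scoring rule. On timing it says: "We will measure all outcomes at the patient level, at baseline when meaningful, and after six months of allocation". Table 1 marks adherence to prescribing guidelines at both T0 and T6.

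Table A1 has four drug rows (ACE-I, ARB, beta-blocker, spironolactone), with the word OR between the first two. Each row has three cells:

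- **2 points:** the target dose. The spironolactone cell reads "Not indicated or Target Dose".
- **1 point:** "Used below 50% of the Target Dose". The ACE-I cell says the same in nearly identical words and carries a citation (reference 49).
- **0 points:** the drug is not used.

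The footnote states "Range: 0 to 8 points".

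Table 2 records the dose of each of these drugs as a number, for example "Beta-blockers dose". Section 3.1 says the health-record data are collected again six months after allocation.

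**The concern.** The three cells do not cover all doses. The 1-point cell stops at 50% of target and the 2-point cell is the target itself, so nothing lies between them. Because doses are recorded as numbers, any prescription in that band will appear in the data with no score attached.

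The article prints the whole scoring rule and makes it the outcome definition. The problem is therefore a stated rule that fails when followed, not a detail left to an analysis plan. Whoever derives the score must either add a rule the article does not contain (1 point or 2) or treat the patient as missing. The first option changes totals. The second makes missingness depend on arm if the band is more heavily populated in one arm than in the other.

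**Working it through.** **1. Inputs.** The point values, cell wording and range come from Table A1, and the numeric dose fields from Table 2. The share q of patient-item pairs falling in the gap is not given anywhere. It is assumed below at 10%, 20% and 40%.

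**2. The plan's own figure.** Adding all four rows gives 4 × 2 = 8, which matches the stated range of 0 to 8. Taking the table's OR literally leaves three items (ACE-I or ARB, beta-blocker, spironolactone), so the maximum is 3 × 2 = 6. The printed range and the printed layout do not agree. The totals below count ACE-I or ARB as one item.

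**3. Literal mapping of dose, as a percentage of target, to points.**

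| Dose | Points |
|---|---|
| 0% | 0 |
| 1%, 25%, 49% | 1 |
| 50%, 60%, 75%, 99% | no cell |
| 100% | 2 |

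Read strictly, a dose above target has no cell either. That is marginal, and nothing here rests on it.

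**4. Profiles.** With four dose states per item (none, below 50%, 50% to below target, target) and three items there are 4³ = 64 profiles. Those with no item in the gap number 3³ = 27, so 64 − 27 = 37 have no total.

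**5. One patient in the gap on all three items.** As written there is no total. If the gap earns 1 point per item the total is 3 × 1 = 3. If it earns 2 the total is 3 × 2 = 6.

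**6. Share of patients with no total.** With k dose-dependent items, independent and with the same q, the share is 1 − (1 − q)^k. Three items apply when spironolactone is scored on dose. Two apply when it is not indicated and takes its 2 points automatically.

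| q | k = 3 | k = 2 |
|---|---|---|
| 10% | 1 − 0.9³ = 27% | 1 − 0.9² = 19% |
| 20% | 1 − 0.8³ = 49% | 1 − 0.8² = 36% |
| 40% | 1 − 0.6³ = 78% | 1 − 0.6² = 64% |

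Independence matters. If a patient's items always fell in the gap together, the share would be q itself (10%, 20%, 40%). For comparison, section 2.11.2 anticipates under 5% missing values. With three independent items, q = 1.7% already gives 1 − 0.983³ = 5.0%.

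**7. Effect on the comparison between arms.** Moving the gap from 1 point to 2 raises an arm's mean by 3 × q × 1 point. The between-arm difference therefore shifts by 3(q_intervention − q_control). With shares of 40% and 20% this is 3 × (0.40 − 0.20) = 0.6 points. With equal shares it is zero.

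**The case against.** The strongest counter-argument concerns consequence. Section 3.2 and the Introduction call guideline adherence exploratory. The abstract lists it as secondary, but section 2.11.2 treats secondary and exploratory results alike as hypothesis-generating and rests the main conclusions on the primary outcome. That stands: nothing here can change the trial's main conclusion.

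Several stronger readings are tempting, and the documents do not support them:

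- **That the choice of boundary alone can create or remove an effect of up to 1.2 points.** A reader might take 3q (0.3, 0.6 or 1.2 points) as the effect at stake. That is the shift in one arm's mean. The comparison moves only by the difference in shares between arms, which the documents do not give.
- **That the unscored band is a common prescription, or the one the intervention will move patients into.** The feasibility data in section 2.2 report essential therapy in 19% of patients but no dose distribution. Section 2.4 describes feedback on clinical management and does not mention up-titration. Both ideas are inference.
- **That this score is the only way to see prescribing.** Individual drug doses are recorded and the record data are collected again at six months, so prescribing can be described without the composite.
- **That someone could pick the convenient boundary.** Section 2.8 has two independent blinded statisticians working with coded groups, and conclusions drawn before unblinding. A late choice would still be post hoc, but it should not be made knowing the arm.

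The intended cut may also be in a source the table cites, or the rule may be settled in an analysis plan not shown here. Either would make the repair easy. Neither alters the printed table, which is the outcome definition the article gives and which no other section completes. The same wording recurs in all four rows, so a fault in reading the PDF is unlikely.

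**Conclusion.** The point holds in limited form. As printed, Table A1 leaves every dose from 50% to just under target without a score, in all four rows. For an affected patient the consequence is no total, or a total that varies by up to 3 points (3 versus 6) with an unstated choice, counting ACE-I or ARB as one item.

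At trial level the size is unknown. The percentages without a total are illustrations that assume a common q and independent items. The shift in the between-arm difference is zero if the arms have equal shares in the gap and 0.6 points at assumed shares of 40% and 20%. Dropping unscored patients would make missingness depend on arm only if the shares differ. Only an exploratory, hypothesis-generating outcome is affected; the primary outcome is untouched.

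**What to change.** Reconcile Table A1 with the source it cites, and reword the cells so that they are exhaustive and mutually exclusive in every row, with each recorded dose mapping to exactly one score. Two wordings would do this: the 2-point category starts at the 50% line, or the 1-point category extends to any dose below target. The sponsor must say which was meant. Fix the rule before any six-month prescription is scored, apply it identically at baseline and at six months, and report the alternative boundary as a sensitivity analysis.

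In the same edit, state whether ACE-I and ARB count as one item and bring the printed range into line with the answer.

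The cost is a short change to one table. No new data are needed, because the drug doses are already collected. The change concerns the scoring rule only, not which dose any patient should receive.

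### The Treatment Adherence Score is given a range of 0 to 8, but its items add up to at most 6, and its dose bands give no score from 50% to under 100% of target dose

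*Protocol article*

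**What the plan says.** Section 3.2 of the protocol article names the outcome and its instrument: "An exploratory outcome will be physicians’ adherence to guidelines, comparing prescription data to guidelines and quality standards using a compliance score". It points to Table A1 in Appendix B for the score. Table 1 schedules the assessment at T0 and at six months. Sections 1 and 3.2 call the outcome exploratory, whereas the abstract lists it among the secondary outcomes.

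Table A1 has four rows, with columns worth 2, 1 and 0 points:

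- ACE-I: target dose (2), "Used below 50% of Target Dose [49]" (1), not used (0).
- ARB, joined to the ACE-I row by OR: target dose (2), "Used below 50% of the Target Dose" (1), not used (0).
- "Beta-blockers use", joined to the above by AND: the same three bands.
- Spironolactone: "Not indicated or Target Dose" (2), then the same 1-point and 0-point bands.

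The footnote reads "Range: 0 to 8 points". Nothing else in the article adds a scoring rule or defines target dose as a range.

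**The concern.** Two features of the printed table do not work. The stated maximum does not follow from the items, and the dose bands are not exhaustive.

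The first leaves it unclear whether the ACE-I and ARB rows are alternatives or are both added. The second matters more. It leaves part of the dose scale without a score, and that part is where a patient sits when treatment has been increased but has not reached target. Cardiologist advice could plausibly produce such changes, so the gap falls where the instrument should be able to register movement between baseline and six months. Two analysts who follow the table faithfully could score the same prescription differently, or leave it unscored.

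This is not a case of detail left to a fuller document. The article prints what is presented as a full scoring table, and that table disagrees with its own footnote and omits a dose band.

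**Working it through.** **Inputs** (all from Table A1): four rows; 0, 1 or 2 points per row; OR between ACE-I and ARB; AND before beta-blocker and spironolactone; stated range 0 to 8.

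**Step 1: reproduce the stated maximum.** Adding all four rows without regard to the OR gives 4 × 2 = 8, which matches the footnote. It would require a patient to hold full points for ACE-I and for ARB at the same time.

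**Step 2: apply the OR as printed.** All combinations of row scores (each 0, 1 or 2) were enumerated under three readings:

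| Reading | Rule | Range |
|---|---|---|
| ACE-I/ARB as one item | max(ACE-I, ARB) + beta-blocker + spironolactone | 0 to 6 |
| Four rows, only one of ACE-I/ARB in use | the unused row scores 0 | 0 to 6 |
| All four rows added | OR ignored | 0 to 8 |

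Both readings that respect the OR give 2 + 2 + 2 = 6. Only the reading that ignores it gives 8.

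**Step 3: test whether the dose bands are exhaustive.** Let f be the prescribed dose as a share of target dose. The bands as worded give:

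| f | Score |
|---|---|
| 0% | 0 |
| 25% | 1 |
| 49% | 1 |
| 50% | none |
| 75% | none |
| 99% | none |
| 100% | 2 |

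The interval 50% ≤ f < 100% has no score. The same wording is used in all four rows, so the gap is present for every drug in the score.

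**Step 4: size of the ambiguity.** If the middle band were given 1 or 2 points, the choice would move a patient by 2 − 1 = 1 point for each drug in that band. The article gives no dose distribution, so the share of patients affected, and any effect on the comparison between arms, cannot be calculated.

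**The case against.** The strongest reply concerns weight. The range error alone changes little. If the OR is applied, each patient's score and the difference between arms are the same whatever the footnote says. The article sets no threshold on the score. That stands: the range is mainly a labelling correction, although it has to be made because the label contradicts the rule.

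The dose-band gap may be one of wording. The 1-point ACE-I cell carries a citation, and if that source counts 50% or more of target as attained, the bands would be complete. The source is not at hand and the article states no such definition. What can be said is that the table as printed does not score that band, not that no scoring rule exists anywhere.

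Four stronger readings are tempting, and the document does not support them.

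- *A fully compliant patient would read as 75% (6/8).* The article never expresses the score as a share of 8.
- *The ambiguity is worth 3 of 6 points.* That needs all three drugs of one patient to fall in the unscored band at once. It is a single-patient worst case and says nothing about the difference between arms.
- *Analysts would pick the missing score in favour of one arm.* Section 2.8 has two independent blinded statisticians working with arms coded A and B, and an analysis plan that is not shown may settle the rule. Blinding limits bias from a late choice, but it does not make the printed score reproducible.
- *Crediting absence of indication only for spironolactone is an error, because the trial enrols every kind of patient.* The supporting sentence is "We will include all adult patients with confirmed heart failure of all aetiologies, regardless of comorbidities or clinical status". It speaks of aetiology, not of whether a given drug is indicated. How a score treats indication is a design preference, and Table 2 has no field for indication, so extending the rule could need new data.

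**Conclusion.** The point holds in two parts. Under the OR as printed, the Treatment Adherence Score runs from 0 to 6, not 0 to 8. A dose from 50% to under 100% of target has no score in any row, so adherence cannot be scored from the table as printed for patients in that band.

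The conclusion rests on reading OR as making ACE-I and ARB alternatives, and on taking target dose to mean the full target because no other definition is given. A definition in the cited source could close the second gap once it is stated.

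The consequence is limited. Section 2.11.2 treats secondary and exploratory results alike as hypothesis-generating and rests the main conclusions on the primary outcome, so the differing status of this outcome in the abstract does not raise the stakes. The primary outcome and the sample size are not touched. The correction is still worth making, because this is the only instrument named for guideline adherence and the repair is cheap.

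**What to change.** Amend Table A1 before any outcome data are seen:

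1. Reconcile the stated range with the OR. With the OR as printed, the range is 0 to 6. Changing the OR merely to preserve the figure of 8 would alter the scoring logic to suit a footnote and is not advised.
2. Reconcile the dose bands with the cited source, and define target dose in the table, so that every recorded dose maps to exactly one score. Which score the band from 50% to under 100% of target receives is for the sponsor's clinicians; this review proposes none.

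The cost is an edit to one appendix table, with the same rule carried into the analysis plan. No new data are needed for these two changes: Table 2 already records doses of ACE-I, ARB, beta-blocker and spironolactone, and Section 3.1 repeats the health-record collection at six months.
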